#### CH study

The primary endpoint in the CH study will be the detection of any developmental abnormality within 2 years of birth. The children in the study are born to women from the PW study or to mothers with proven ZIKV infection during pregnancy. The two-year follow-up brings up the practical restriction of drop-outs as right censoring. Consequently, the primary endpoint will be analysed with survival analysis techniques. Predefined basic variables on the outcome will be included in a Cox model with region as a random factor. Specific developmental abnormalities, which are only measured at one follow-up visit, will be evaluated by mixed logistic models, containing the respective variables, with region as a random effect as above.

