**Table Tabb:** 

**Children cohort (CH;** **clinicaltrials.gov** **identifier: NCT03393286)** **Primary Objectives** 1. To estimate the absolute and relative risks of developmental, neurological, ophthalmic, and auditory abnormalities during the first 2 years of life in children born to women infected with Zika virus (ZIKV) during pregnancy compared to women not infected during pregnancy 2. To describe the spectrum of abnormalities and clinical course during the first 2 years of life in children born to women with ZIKV, dengue virus (DENV) Chikungunya (CHIKV) or possibly other arbovirus infections during pregnancy **Secondary Objectives** 1. To evaluate risk factors for developmental abnormalities in children exposed to ZIKV during pregnancy 2. To describe the incidence of ZIKV infections after birth in early childhood and evaluate the associated risks for abnormal child development; 3. To determine the incidence of ZIKV infection in the mother after birth and evaluate its clinical features as well as its kinetics in different body fluids 4. To determine the rate and risk factors and effect modifiers for congenital, perinatal and postnatal mother-to-child transmission of ZIKV 5. To describe the kinetics and evolution of infection and immune responses to ZIKV infection in infants and children, stratified by transmission pattern (for example in utero vs. post-natal) **Inclusion/exclusion** (Fig. 3) Inclusion criteria • Group A: Infants born to mothers with confirmed ZIKV infection during pregnancy • Group B: Infants born to mothers with confirmed DENV, CHIKV or other arboviral infection during pregnancy (detected in incident fever/rash episodes) • Group C: Random sample of infants born to mothers without ZIKV/DENV/CHIKV or another arboviral infection during pregnancy (from ZIKAlliance PW cohort), 1:1 proportion compared to groups A and B together. The remaining children from mothers who were not infected with any of the three arboviruses are followed in Group D (standard visitation schedule) • Mother-infant pairs available to undergo study visits and procedures • Written informed consent (assent form and consent by a legal guardian if applicable) Exclusion criteria • Mother aged below 16 years old **Endpoints** • Infant developmental abnormalities as assessed by neurological examination, Ages & Stages Questionnaire® and Bayley Scales of Infant Development	

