#### Study design

CH of women exposed to ZIKV during pregnancy, and a subset of those not exposed, will be followed after birth for developmental milestones (neuro-cognitive, motor, ophthalmic, and auditory defects) and also to assess the risk of post-natal ZIKV infection among susceptible infants. We will also follow CH of women with incident arboviral infection (including DENV, CHIKV or other such as YF) detected in symptomatic fever/rash episodes over the course of the pregnancy.

At delivery (last visit of PW study), investigations of the mother will include a full blood count, serological tests for ZIKV as well as RT-PCR-testing in blood and urine for ZIKV. The presence of potential environmental pollutants will be tested in a subsample of PW from appropriate biological materials. In addition, placenta and umbilical cord tissue, cord blood, and amniotic fluid will be collected. All biological material will be collected and stored according to detailed SOP. TORCHS and HIV testing will be carried out according to national guidelines and, if not available, may be performed in stored samples for the purposes of the study.

The investigations performed on the infant at birth will include a standard neonatal examination comprised of Apgar scores, anthropometry, reflexes and muscle tone, and collection of blood via heel prick or venepuncture if necessary. Screening tests will be carried out at birth according to national guidelines. Additional investigations, such as cerebral imaging or collection of cerebrospinal fluid, will be carried out only if medically indicated.

Follow-up visits will be scheduled at ages 1–3, 4–6, 12, and 24 months to assess the infant’s development using comprehensive neuro-developmental evaluation instruments (Ages & Stages Questionnaire [ASQ-3] and Bayley Scales of Infant Development) [42, 43]. Blood and urine samples from the infant will be collected to test for ZIKV infection (using RT-PCR) or seroconversion. In the mother, we will also test blood and urine samples, with added testing of saliva and breast milk in breastfeeding women who test RT-PCR-positive in urine or blood. CH with any abnormalities detected at birth or during follow-up will be managed according to national protocols.

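### The Children cohort's primary endpoint is detected at visits and so interval-censored, but the named Cox model allows only for drop-out; its hazard ratio is biased if exposure groups are examined at different ages

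*Protocol article*

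**What the plan says.** Under Data analysis, CH study, the protocol article defines the outcome: "The primary endpoint in the CH study will be the detection of any developmental abnormality within 2 years of birth". Box 2 says how it is ascertained: "Infant developmental abnormalities as assessed by neurological examination, Ages & Stages Questionnaire® and Bayley Scales of Infant Development". The CH Study design section fixes when: "Follow-up visits will be scheduled at ages 1–3, 4–6, 12, and 24 months". The first two visits have printed windows of two months; the 12- and 24-month visits have none.

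The CH study paragraph names one complication of the time axis: "The two-year follow-up brings up the practical restriction of drop-outs as right censoring". From this it concludes that survival methods are needed, and specifies: "Predefined basic variables on the outcome will be included in a Cox model with region as a random factor". It recognises visit-bound measurement only for secondary analyses: "Specific developmental abnormalities, which are only measured at one follow-up visit, will be evaluated by mixed logistic models".

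In Box 2, Group A is the ZIKV-exposed infants. Group C is a random sample of unexposed infants at a "1:1 proportion compared to groups A and B together". The remaining unexposed children form Group D, on a schedule labelled as standard. The article does not say how that schedule differs or whether Group D enters the model.

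**The concern.** The event is detection, so its date is largely the date of an examination. True onset lies somewhere after the last negative visit, and between the later scheduled visits that gap is 6 or more months and then 12 months. These are interval-censored data, and the stated reason for choosing Cox (right censoring by drop-out) does not address that.

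The harm arises at the 24-month visit if age is used as recorded. Children found normal leave the risk set on the day they are seen. If exposed children are seen slightly earlier, their events are set against many unexposed children who count as at risk but have not yet been examined. The later events among unexposed children then face a risk set from which most exposed children have gone. The hazard ratio rises although the risks are equal. If exposed children are seen later, it falls. The estimate at stake is the relative risk in the cohort's first primary objective.

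**Working it through.** **Inputs from the article:** the visit ages, the detection endpoint and the Cox model. The article gives no expected risk, group size or effect for the CH analysis. Its only power statement concerns microcephaly and plays no part here.

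**Assumptions:** 500 exposed and 500 unexposed; new detections of 3, 3, 4 and 8% at the four visits; 24-month visit age with SD 1 month; a mean difference of 0 to 1 month in age at examination; two-sided 5% tests.

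**1. The mechanism in its limiting case.** Take equal groups with equal risk, and let every exposed child have the 24-month visit before any unexposed child. Let d events occur at that visit in each group.
- When a fraction x of the exposed remain, the exposed share of the risk set is x/(1 + x). Its average over x from 0 to 1 is 1 − ln 2 = 0.307.
- Events in unexposed children occur when no exposed child remains, so they add an expected 0.
- The null expectation of exposed events is 0.307d, against d observed. With 8% of 500, d = 40 and the expectation is 40 × 0.307 = 12.3.
- On a common visit time it would be 0.5 × 2d = 40, equal to the observed number.

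**2. Overlapping visit ages, true hazard ratio 1.** This is Cox on age at detection, with event-free children censored at their own visit. The ranges cover repeated simulations under the assumptions above.

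| Exposed seen earlier by | Cox hazard ratio | False-positive rate |
|---|---|---|
| 0.25 month | 1.09–1.12 | 11–12% |
| 0.5 month | 1.15–1.22 | 23–26% |
| 1 month | 1.43–1.47 | 56–64% |

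With exposed children seen 0.5 month later, the hazard ratio is 0.82–0.83, and a true value of 2 is estimated as 1.64–1.68. With a visit SD of 0.5 month, a 0.5-month shift gives 1.45–1.46.

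**3. A different set-up.** Here onset occurs at a constant rate, two-year unexposed risk is 10% or 30%, visits fall uniformly within 1 month either side of 2, 5, 12 and 24 months, and all four visits are shifted. For a true value of 1, shifts of 0, 0.25, 0.5 and 1 month give Cox hazard ratios of 0.97, 1.26, 1.50 and 1.84 at 10% risk, and 1.00, 1.25, 1.43 and 1.82 at 30% risk. A true value of 2 is estimated as 3.6 to 4.0 at a 1-month shift.

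**4. What does not drive the bias** (true value 1 unless stated)
- Equal timing: 0.97–1.03.
- Differences confined to the two early windows, with 12 and 24 months fixed: 0.99–1.00.
- Unexposed children seen only at 12 and 24 months: 0.99–1.07.
- Ties: with nominal ages and Efron ties, a true value of 2 is estimated as 1.95–2.00. Breslow ties give 1.86, but only with detection raised to 5, 5, 10 and 20%.

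**5. Remedies on shifted data**
- Discrete-time complementary log-log model on visit number, set-up of step 2: 0.98–1.02 for a true 1 and 1.96–2.01 for a true 2.
- The same model, set-up of step 3: 0.93–1.00 for a true 1 (rejection 4–12%) and 1.90–2.01 for a true 2. The low values occur where unexposed children have extra time in which to develop an abnormality.
- Cox on nominal visit ages, shifts of 0.5 and 1 month: 1.00 and 0.99 (rejection 7% and 6%).
- Cox with event-free children censored at a common time after the visit window, same shifts: 1.00 and 1.03 (4% and 5%).

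**The case against.** A reader might infer that the ZIKV hazard ratio will in part measure which group was examined first. The article does not support that. It prints one visit schedule for the cohort, draws Group C at random from the unexposed infants and describes common protocols and operating procedures. Nowhere does it say that Groups A and C are seen at different ages, and with equal timing Cox is essentially unbiased. Nor can the two-month early windows, or tie handling, be blamed as the main cause.

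It is also fair to say that the bias comes from a convention, not from Cox as such. The article fixes neither the time scale nor the censoring date of event-free children, and nominal visit ages or a common censoring time remove the problem. Such details may sit in the full protocol or the analysis plan, and the article calls its analysis exploratory. Every magnitude above rests on assumed risks, group sizes and shifts.

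All of this stands, and it limits the point to a conditional one. It does not remove it. The article names the model for the primary endpoint and gives a reason that overlooks how the endpoint is observed. Unequal timing is also plausible. Exposure is not randomised, and the CH study paragraph admits children of mothers with proven infection as well as those from the Pregnant Women cohort. Enrolment may move between areas, no window is printed for the two visits that matter most, and Group D's schedule is not explained.

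**Conclusion.** The point holds in conditional form. The primary endpoint is mainly visit-detected and therefore interval-censored, while the stated method considers only right censoring. Some abnormalities may be seen at birth, so detection is not confined to the four visits.

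The bias needs two things together: an analysis on actual age at detection, with event-free children censored at their own last visit, and a difference between exposure groups in age at the later visits. Under the step 2 assumptions, a difference of 0.5 to 1 month then gives a hazard ratio of about 1.15 to 1.45 where the truth is 1. The set-up of step 3 gives about 1.4 to 1.8. The direction depends on which group is seen first. If either condition is absent, the bias is negligible. Weight: moderate, a cheap improvement and not an essential correction.

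**What to change.** Replace the Cox sentence for the CH primary endpoint with one of these:
- a discrete-time complementary log-log model with scheduled visit number as the time axis and region as a random effect;
- a proportional hazards model for interval-censored data, using each child's last negative and first positive visit (not simulated here);
- the Cox model kept, but on nominal visit time with Efron or exact ties.

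For the discrete-time or nominal-time analysis, assign each assessment to its scheduled visit, so that a late 24-month visit still counts. State how Group D's schedule differs from that of Groups A to C, and whether Group D enters the model.

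The cost is a paragraph of wording, slightly more analysis work and, for the discrete-time and nominal-time versions, no use of exact detection ages. No new data are needed. A discrete-time model does not adjust for a real difference in time available for onset; in step 3 the largest effect of this was a hazard ratio of 0.93 for a true 1, at a 1-month shift and 10% risk.

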#### NH study

The NH study will be carried out at a subset of the sites including participants who experience acute rash/fever illness, suggesting arboviral aetiology. The sample size will depend on the local epidemiology. The statistical analysis will be largely descriptive and informed by prior studies of arboviral rash and febrile illness [14, 82]. The prospective nature of the study will be used to describe the trajectory over time of signs and symptoms, and hence further define the case definitions of arbovirus infections, including ZIKV.

### Harmonisation, clinical monitoring, ethics, and dissemination

The multicentre cohort studies were built on standardized common protocols as well as a series of SOP to ensure systematic and homogenous execution of clinical and laboratory study procedures and sampling. Harmonisation of protocols for clinical cohorts as well as diagnostic algorithms has been ongoing between members of the ZIKAlliance consortium and other currently active research programs, funded for example by the EC or by the National Institutes of Health (NIH). The benefit of this is that patients can be enrolled and studied outside of ZIKAlliance with compatible protocols, which were made publicly available [83], and a pooled dataset may later be analysed for the maximum benefit.

Clinical monitoring is integrated into the programme of work from the outset, ensuring compliance with Good Clinical Practice (GCP) standards. The studies are conducted in accordance with the International Conference on Harmonisation - GCP guidelines. A reciprocal clinical monitoring network was set up between the partners of the Consortium as part of preparedness and capacity building.

The observational studies outlined here are conducted in accordance with the principles of the Declaration of Helsinki, the Nagoya protocol, GCP and relevant local regulations. All procedures employed in the clinical and related laboratory studies comply with local and international legislations regarding research involving human subjects, biobanking, and shipping of specimens. The protocols, amendments, consent and assent forms have been submitted to the relevant Research Ethics Committees at each study site, and to relevant regulatory authorities for written approval.

In the case of a clinical episode suggestive of ZIKV, the national standard of care and visitation schedule will be followed. The study team is in close contact with national authorities and will inform the surveillance teams about trends of confirmed infections per site. Unexpected incidental findings (not related to ZIKV or other arboviral infections) may occasionally be identified in individual patients in the course of the clinical study. The patient and/or parent/guardian will be informed, and with their consent, a referral will be made to an appropriate clinic or health facility for further investigation or longer-term follow-up.

Study results will be fed back to participants through periodic reports, and relevant results will also be communicated to healthcare professionals and health authorities. Scientific dissemination will not make use of professional writers and publications resulting from the study will use prevailing authorship eligibility guidelines [84]. It will be stated that the EC has no role on study design, data collection, analysis, interpretation of results, manuscript writing or decision to publish resulting reports.

## Discussion

After 2018, ZIKV transmission is projected to be low in the major urban areas of Latin America [85] until susceptibles have built up after approximately 10 years [5]. In the meantime, the results of these large cohort studies will provide better risk estimates for birth defects and other developmental abnormalities associated with ZIKV infections including possible co-factors that explain the variability of risk estimates currently seen between the Northeast of Brazil and other countries and regions. The ZIKAlliance Consortium covers a broad geographic region in Latin America and the Caribbean in order to represent the different environmental and demographic conditions that may influence the development and outcome of the ZIKV epidemic. These data will help decision-makers to allocate prevention and health care resources according to severity and impact of the epidemic. In addition, the results will provide a historical baseline for future intervention trials, should a vaccine or therapeutics become available and be tested without a control arm, as has recently been done in Ebola vaccine trials [86].

## Data Availability

The datasets used and/or analyzed during this study will be available from the corresponding author on reasonable request.

## Abbreviations

CH: Children
CHIKV: Chikungunya
CRFs: Case report forms
CZS: Congenital Zika syndrome
DENV: Dengue virus
ECLAMC: Latin American Collaborative Study on Congenital Malformations
EC: European Commission
EQA: External Quality Assurance
GCP: Good Clinical Practice
HH: Household
NH: Natural history
NIH: National Institutes of Health
PW: Pregnant women
RT-PCR: Reverse transcriptase PCR
TORCHS: Toxoplasmosis, Rubella, Cytomegalovirus, Herpes and Syphilis
VNT: Virus neutralisation
WHO: World Health Organization
WPs: Work packages
YF: Yellow fever
ZIKV: Zika virus
